#### Exercise uptake and physical activity maintenance

Exercise participation after completion of the structured supervised program – 3 months to 9 months

After completion of the 12 week program, participants are expected to be familiar with the equipment, the exercises and their physical abilities and therefore able to exercise independently and safely if they choose to do so. At the completion of the structured 12 weeks exercise program participants will be given two options to choose from to continue their physical activity.

Option 1 – independent unsupervised access and usage of the exercise park in participants’ own preferred time, free of charge.

Option 2: access to twice a week supervised exercise sessions on the exercise park with a potential cost of $5–8 per session. The inclusion of cost will be dependent on the participating council and will be equivalent to the price that older adults would have to pay to attend a group exercise program that is publicly subsidized through community health services in Australia. Hence, this option is to simulate what the likely cost and participation for an ongoing group program in real life. During this 6 month follow-up period, participants will be informed of weekly times when the exercise instructors will be available at the Senior Exercise Park. Participants can then attend on their preferred time/sessions. At these sessions, the exercise instructors will supervise participants and provide advice regarding exercise progression to fit individual’s progression needs.

#### Participation rate (adherence) and exercise monitor

##### During the 12 weeks supervised exercise program

Frequency of physical activity will be determined from daily attendance logs kept by the exercise instructor. Overall adherence to the structured exercise program will be defined by the number of sessions attended: where 100% adherence is if participant attended 24 sessions.

##### Monitoring exercise uptake following the 12-week exercise program for 6 months – fob access system

Adherence and exercise uptake for 6 months post intervention will be monitored using a fob access system (CityWatch Security, Victoria Australia). The fob access system will include a scanner/card reader (Asperio RF card reader) installed at each site (mounted on a bollard), a control panel (Integriti Control Panel) within a secure cabinet installed at a location (external wall) nearby to the card reader (receives signals from the RF card to the control panel), and specialized software (Integriti Professional Software) installed in the head office (National Ageing Research Institute researchers’ office). Participants will then be assigned their individual identification key (fob) which they will be able to tap at the card reader each time they access the Senior Exercise Park. Their access will then be recorded and monitored (thereby electronically monitoring access).

### Safety considerations and adverse events

#### Weather elements

In extreme weather conditions (e.g. heavy rain, extreme heat (above 30 °C)) if deemed by the exercise instructor as unsafe to exercise, sessions will be cancelled. Our pilot study results in Melbourne indicated that weather did not affect overall adherence (80%) for the exercise sessions with less than 10% of sessions cancelled [10]. In summer in Melbourne, classes will be conducted in the morning and late afternoon (to avoid the high temperatures around the middle of the day), and shade-cloth cover and/or other sun-smart behaviours will be facilitated. Participants will be encouraged to bring their own sunscreen and water to sessions (although these will also be available from the exercise instructor at supervised sessions). In circumstances where sessions will be cancelled, or during a holiday period, makeup sessions will be organised towards the end of the program (up to two weeks or 4 sessions).

#### Adverse events

##### Muscle soreness

Following the exercise sessions, short duration muscle soreness will be expected and is a typical response of the body to exercise in people who have done little or no exercise, or people who are performing an unfamiliar type of exercise. Instances of severe muscle soreness reported by the participant will be recorded.

##### Falls

Any falls during the delivery of the structured supervised exercise programs and during the independent usage phase of the Senior Exercise Park will be recorded.

##### Cardiorespiratory adverse reaction

Any report of difficulty breathing that does not settle quickly with rest, new or unrelenting chest pain, or acute changes in the level of consciousness during the session, may precede a serious medical emergency such as cardiac arrest or stroke. In this event the session will be stopped immediately and an emergency response will be initiated. A potentially serious event will be defined if the participant reported difficulty breathing but symptoms settled quickly with rest and their clinical signs (respiration rate, heart rate, oxygen saturation) remain normal. The participant will be able to elect to complete the session provided these symptoms settled quickly with rest and clinical signs remain normal. A serious adverse event will be defined if symptoms have not settled and medical emergency care was required. All adverse events will be recorded.

### Sample size calculation

The power calculation is based on increasing physical activity level (CHAMPS) by the end of the 9 month follow-up period. A previous study using the CHAMPS reported mean differences of 687 (SD difference 1509) and 487 (SD difference 1196) energy (calories) expenditure per week in all activities and in moderate intensity activities respectively following 6 months physical activity program for older people [15, 36]. To account for any potential variation between the ENJOY exercise park program and the latter reported community physical activities as well as potential variation in the sample population (people from different multicultural backgrounds) [37] a reduction of 20–25% (500 and 400 cal/week in all activities and in moderate intensity activities respectively) was applied to these outcomes. Using this conservative approach, an effect size d = 0.33, 90% power and alpha =0.05,a sample size of 98 participants is required (G*Power, two tail). To account for potential 15% drop out, a sample of 113 will be recruited. As such, we aim to recruit a sample of 37–38 participants in each participating site.

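### The recruitment target of 113 multiplies 98 by 1.15 instead of dividing by 0.85, so 15% dropout leaves about 96 completers rather than 98: a minor arithmetic slip with little effect on power

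*Protocol article*

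**What the plan says.** All the figures are in the Sample size calculation section of the protocol article. Sizing is for the change in CHAMPS physical activity by 9 months in a single-group pre-post design. An earlier study using the same questionnaire supplies "mean differences of 687 (SD difference 1509) and 487 (SD difference 1196) energy (calories) expenditure per week", for all activities and moderate-intensity activities in turn. The mean changes are then discounted to "500 and 400 cal/week in all activities and in moderate intensity activities respectively". From these the article derives "an effect size d = 0.33, 90% power and alpha =0.05,a sample size of 98 participants is required (G*Power, two tail").

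The dropout allowance follows: "To account for potential 15% drop out, a sample of 113 will be recruited". The total is then spread over the sites: "we aim to recruit a sample of 37–38 participants in each participating site". The Exercise Park intervention section lists three sites. The Statistical analysis section plans multiple imputation for missing 9-month data. The article does not give the formula used to get from 98 to 113.

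**The concern.** A dropout allowance should be set so that the number left after the assumed loss is at least the number the power calculation calls for. Dropout applies to everyone recruited, so the required number is divided by one minus the dropout rate. Adding 15% of the required number to itself gives a target that is slightly too small, because the later loss is 15% of a larger base. The figure 113 looks like the result of that shortcut.

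At stake is the internal consistency of the sample size statement: a reader who applies the stated dropout to the stated target does not get back to the stated requirement. The error runs in the unfavourable direction, so how much power it costs needs to be checked.

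**Working it through.** **Inputs (all from Sample size calculation).** Two-sided alpha 0.05; power 90%; mean change 500 with SD of change 1509 (all activities); mean change 400 with SD of change 1196 (moderate intensity); rounded d = 0.33; required number 98; dropout 15%; recruitment target 113.

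**Step 1: reproduce 98.** For a paired comparison, d = mean change / SD of change:

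- all activities: 500/1509 = 0.3313
- moderate intensity: 400/1196 = 0.3344

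Power comes from the noncentral t distribution with n − 1 degrees of freedom and noncentrality d√n, two-sided at 0.05. The smallest n reaching 90% is 98 for d = 0.3313, 96 for d = 0.3344 and 99 for d = 0.33. The published 98 is therefore reproduced exactly from the all-activities inputs. It is a number of participants with both measurements and contains no hidden dropout allowance.

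**Step 2: reproduce 113.**

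- Multiplying: 98 × 1.15 = 112.7, rounded up to 113. This matches the article.
- Dividing: 98/(1 − 0.15) = 98/0.85 = 115.3, rounded up to 116. This does not match.

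**Step 3: apply the stated dropout to the stated target.**

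- 113 × 0.85 = 96.05, so about 96 completers, 2 below 98.
- 116 × 0.85 = 98.6, which meets the requirement.
- Dropout that 113 can absorb with 98 remaining: 1 − 98/113 = 13.3%.

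**Step 4: cost in power, completers only.**

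| Effect size | Power at n = 98 | Power at n = 96 | Difference (points) |
|---|---|---|---|
| 0.33 (rounded) | 89.9% | 89.3% | 0.6 |
| 500/1509 = 0.3313 (all activities) | 90.1% | 89.5% | 0.6 |
| 400/1196 = 0.3344 (moderate intensity) | 90.6% | 90.0% | 0.6 |

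**Step 5: per-site figure.** 113/3 = 37.7, and 38 + 38 + 37 = 113. The range of 37–38 restates the total and adds no error of its own. A total of 116 would be 38–39 per site (39 + 39 + 38).

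**The case against.** The strongest reply is that the slip has no practical consequence, and most of that reply stands. The loss is about 0.6 points of power. At the printed d = 0.33, even 98 completers give 89.9%, so the miss is of the same order as the rounding of the effect size. On the moderate-intensity inputs the 90% target is still met with 96. The 15% is presented as a possible loss rather than a forecast, and 113 tolerates 13.3%. The effect was already discounted: at the undiscounted changes (687/1509 and 487/1196), 96 completers would give 99.3% and 97.7% power. Uncertainty about the effect far outweighs two completers.

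None of this makes the arithmetic right. The article states the requirement, the dropout rate and the target, and they do not agree. This is not a detail that a condensed article has left to a fuller document.

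Three stronger readings are tempting, and the document does not support them:

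- A reader might infer that the trial misses its planned power in general. That is true only for the all-activities inputs and the rounded d, and by 0.5 to 0.7 points. The Statistical analysis section does name the overall activity score as the primary outcome, so 89.5% is the more relevant figure, but the gap is still half a point.
- A reader might take the low end of the site range at every site, 3 × 37 = 111, and find a larger shortfall. That contradicts the stated total of 113.
- A reader might say that multiple imputation recovers nothing from those who drop out. The imputation model is not shown. If it uses 3-month values, people lost between 3 and 9 months could contribute some information. Neither full recovery nor none can be asserted.

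**Conclusion.** The point holds as a minor arithmetic error. The target of 113 comes from 98 × 1.15, whereas 15% dropout calls for 98/0.85 = 116. As written, the plan expects about 96 completers, 2 short of its own 98, and the target is 3 short of the number that would deliver 98.

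Expected power at the stated dropout is 89.5% for all activities, 89.3% at the rounded d and 90.0% for moderate-intensity activities. These figures assume a paired t-test on completers with the article's own means and SDs. The planned analysis is a regression with multiple imputation, so its actual power may differ somewhat, but that does not alter the recruitment arithmetic. Nothing here bears on bias, type I error or the validity of the primary comparison, and calling the trial underpowered because of it would go beyond what the figures show.

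**What to change.** Keep 113 and correct the sentence that links it to dropout, in one of two ways:

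- state that 113 recruits allow for about 13% dropout while retaining 98 completers; or
- keep the 15% assumption and state that it leaves about 96 completers, with about 89.5% power for all activities (500/1509) and 90.0% for moderate-intensity activities (400/1196).

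Either costs one sentence and changes nothing in the conduct of the trial; the per-site figure can stay. For reference, 98/0.85 gives 116, or 38–39 per site. With so little power at stake, recruiting the extra three is not needed to put the statement right.

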### Statistical analysis

For the primary outcome of overall physical activity score and the physical, mental, and health outcome measures, regression analyses with data clustered within individual participants will be used to determine if there are differences between scores collected at baseline assessment and at 9 month follow-up. Moreover, repeated measures analysis of variance will be used to examine the effect of the exercise program on physical activity level, physical, mental and psychosocial and health outcomes between the other time points (baseline, 3 months, 12 months). Information collected about park usage, participant’s feedback and exercise adherence will be reported using descriptive statistics (frequency of usage, % of adherence). The outcome variables will be assessed for normality prior to analysis and transformed accordingly. Data will be analysed using SPSS version 25.0 (IBM Corp, NY, USA). Multiple imputation will be used to account for missing data at the 9 month follow-up assessment.

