**Table 1 Tab1:**
[figure not shown]
ENJOY study procedure

Abbreviated Mental Test Score (AMTS), a set of 10 questions to assess cognitive impairment (memory), will be administered on the initial assessment [14]. Participants who score < 7/10 will be excluded from the study. Participants will then be asked to complete the Exercise and Sport Science Australia (ESSA) exercise screening tool to evaluate any contraindicated medical conditions to exercise: https://www.essa.org.au/wp-content/uploads/2011/09/Screen-tool-version-v1.1.pdf. Participants answering ‘yes’ to any of the screening questions will be required to obtain medical clearance from their general practitioner prior to participation in the exercise intervention.

At baseline, 3 months and 9 months participants will undergo a comprehensive suite of physical (strength, balance, functional mobility) tests, falls risk assessment and falls history, and complete psychosocial (quality of life, enjoyment, social isolation, fear of falls, loneliness), and mental health measures (mental wellbeing, depression). In addition, they will be asked to provide feedback and complete satisfaction surveys (survey 1 and 2). Health cost/services data will also be collected (health economic evaluation). At 12 months, a final assessment will take place (via phone and or mail postage) to evaluate health cost/services as part of the health economic data collection. Monthly falls calendars will be collected from baseline for 12 months.

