##### Health care resource use and productivity

Health care costs will be measured using Medicare and Pharmaceutical Benefits Scheme database extractions for publicly subsidized primary health services. Hospitalisations will be measured using participant self-report of diagnosis and days spent in hospital. Productivity costs will be measured using the iMTA Productivity Cost Questionnaire [33] which includes three modules measuring productivity losses of paid work due to 1) absenteeism and 2) presenteeism and 3) productivity losses related to unpaid work. Participants will be asked to complete this questionnaire at baseline and 12 month follow up assessments. Home nursing, allied health and community service use will be captured using self-report. For the 12 month assessment, the form will be posted to the participants in addition to the EQ-5D-5 L. A reply paid envelope will be enclosed so participants can post these directly to the research team.

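### The repeated-measures ANOVA is set at baseline, 3 and 12 months, but on the stated schedule most of the outcomes it names are collected at baseline, 3 and 9 months

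*Protocol article*

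**What the plan says.** The Statistical analysis section of the protocol article sets out two inferential analyses.

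- A regression with data clustered within participants, for the primary physical activity score and the other outcome measures, tests for "differences between scores collected at baseline assessment and at 9 month follow-up".
- For a second analysis, the article states: "repeated measures analysis of variance will be used to examine the effect of the exercise program on physical activity level, physical, mental and psychosocial". The same sentence adds a general health category to that list and then fixes the visits to be compared, which are those "between the other time points (baseline, 3 months, 12 months").

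The collection schedule is given in two places.

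- Procedure: "At baseline, 3 months and 9 months participants will undergo a comprehensive suite of physical (strength, balance, functional mobility) tests", together with the falls-risk, psychosocial and mental health measures. The last contact is described separately: "At 12 months, a final assessment will take place (via phone and or mail postage) to evaluate health cost/services". Its purpose is to supply the economic evaluation.
- Health care resource use and productivity: "For the 12 month assessment, the form will be posted to the participants in addition to the EQ-5D-5 L". The schedule of the productivity questionnaire is also given there: "Participants will be asked to complete this questionnaire at baseline and 12 month follow up assessments".

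**The concern.** The ANOVA names a method, a set of outcomes and three time points, and the third time point does not fit the data that the article says will be collected. The 9-month visit has the full battery but is left out of the repeated-measures analysis. The 12-month contact has almost none of the battery but is included.

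What is at stake is the 3-month result. The regression uses only baseline and 9 months, so the ANOVA is the only stated inferential analysis that takes in the end of the supervised program. If it cannot be run as specified, someone must choose other time points later, possibly with the data in view. In an uncontrolled pre-post study with many outcomes, that choice should be fixed in advance. It also bears on what the trial can say about gain during the 12 supervised weeks and maintenance over the following six months, because no stated analysis compares 3 with 9 months.

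**Working it through.** The plan gives no figure on this point, so the check sets the named outcomes against the stated visits.

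**Inputs.** Scored measures are taken from the Assessments section. Visits are taken from Procedure, Health care resource use and productivity, and Sample size calculation.

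| Measure | Number | Stated visits | Value at 12 months? |
|---|---|---|---|
| Physical function tests (30-s sit to stand, two-minute walk, step test, 4 m walk) | 4 | baseline, 3, 9 months | No; they cannot be done by phone or mail |
| EQ-5D-5L | 1 | baseline, 3, 9 months, plus the 12-month posting | Yes |
| WHO-5, UCLA loneliness, GDS-15, Short FES-I, PACES, Lubben | 6 | baseline, 3, 9 months (constructs listed in Procedure) | None stated |
| Self-Efficacy for Exercise | 1 | not listed by construct in Procedure; belongs to the psychosocial group in Assessments | None stated |
| FROP-Com | 1 | baseline, 3, 9 months (falls-risk assessment) | None stated |
| CHAMPS | 1 | no visit list in the running text; powered at 9 months | None stated; absence inferred |

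**Count.** The total is 4 + 1 + 6 + 1 + 1 + 1 = 14. One has a stated 12-month value, so 14 − 1 = 13 do not. These 13 are not equally certain:

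- For the 4 timed tests, absence at 12 months follows from the mode of contact as well as the schedule.
- For the 7 other psychosocial and mental health scales and FROP-Com (8 in all), it follows from the running text.
- For CHAMPS, it is inferred from the stated purpose of the 12-month contact, the content of the posted pack, and the 9-month basis of the power calculation.

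**Other outcomes that could fall under the ANOVA's health outcomes.** The productivity questionnaire is given at baseline and 12 months only, so it has no 3-month value and cannot enter a three-visit ANOVA either. Falls calendars run monthly for 12 months, but they give event data and not a visit score. Cost and service data are described at all four contacts.

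**Effect on the primary analysis.** The sample size is based on change in CHAMPS by 9 months. With d = 500/1509 = 0.331, two-sided alpha 0.05 and 90% power, a paired t-test (noncentral t) needs n = 98, which is the article's figure. That contrast uses baseline and 9 months only, so the 12-month mismatch does not reach it.

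**The case against.** The strongest reply is that the formal schedule is in Table 1 and the flow in Fig. 1, and neither can be seen here. The running text is not a complete schedule: it does not list CHAMPS at any visit, so its silence on CHAMPS at 12 months shows little. The Abstract and Design and setting say in general terms that participants are assessed at 3, 9 and 12 months. This stands for CHAMPS and lowers certainty for the questionnaires. It does not rescue the timed tests. If Table 1 did place the other scales at 12 months, it would conflict with Procedure and the two would still need reconciling.

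A second reply is that the bracketed time points merely list the remaining visits, with each outcome analysed where it was collected. That reading is possible but the text does not state it, and under it the 12-month entry would still apply to only one of the 14 scored measures.

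Three stronger readings are tempting, and the documents do not support them.

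- **A reader might infer that the ANOVA cannot be run at all.** It can be run for the EQ-5D-5L, which has baseline, 3-month and 12-month values.
- **A reader might infer that the main result is compromised.** The baseline-versus-9-month comparison has its own regression, and the ANOVA is supplementary to it. Analysing the two separately is valid; a joint model is a better choice but its absence is not an error.
- **A reader might infer that the ANOVA has no protection against missing data**, because the article says "Multiple imputation will be used to account for missing data at the 9 month follow-up assessment" and names no other visit. Stating imputation for one visit does not exclude other handling elsewhere, and such detail for supplementary analyses is commonly left to a statistical analysis plan. The article gives a 15% drop-out allowance and no visit-specific missingness, so no complete-case loss can be derived from it.

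**Conclusion.** The point holds as an internal contradiction between the analysis time points and the collection schedule. The ANOVA cannot be run as written for the four timed physical tests. On the running text it also cannot be run for the scored scales other than the EQ-5D-5L, so 13 of 14 scored measures lack a stated 12-month value. The part of that count beyond the timed tests assumes that Table 1 agrees with Procedure, and CHAMPS rests on inference. The primary contrast and the sample size are not affected. What is affected is the only stated inferential use of the 3-month data. This should be corrected before analysis, because the plan as written leaves the replacement time points open.

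**What to change.** Correct the time points in Statistical analysis so that they match the schedule. The preferred form is one linear mixed model per outcome, with visit (baseline, 3, 9 months) as a categorical factor, all available data used, and 9 months minus baseline as the primary contrast. The same model then gives the changes from baseline to 3 months and from 3 to 9 months. If the ANOVA is kept, move it to baseline, 3 and 9 months.

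Limit 12-month analyses to the EQ-5D-5L and the cost and service outcomes collected then, and treat the productivity questionnaire as a baseline-to-12-month comparison. State the CHAMPS visits in the text. If Table 1 places any other measure at 12 months, amend Procedure to agree.

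The cost is a rewording of the analysis section, plus a line on CHAMPS visits. No extra visits or data collection are needed.
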